#### Collection of isotope samples

Milk volume will be measured at 2–4 week (as baseline data at HV1) and 12–14 week (at HV3) using stable isotopes which allow the measurements to be performed without interfering with the breastfeeding process [32, 34]. To dose the mother, she will be asked to drink approximately 30 g deuterium dilution (^2^H_2_O) through a straw. A maternal baseline salivary sample will be obtained by using a salivette prior to dosing and during the following 14 days post-dose (day 1, 4 and 14). The mother will be asked not to eat or drink for 30 min prior to collecting a saliva sample. Infant urine samples will also be collected at day 0 (baseline sample) and then over 14 days post-dose (day 1, 3, 4, 13 and 14). Detailed instructions on collection of urine samples will be provided and demonstrated to the mother during the first home visit session. To estimate infant total body water, additional urine samples will be collected after administering 10 g deuterium (^2^H_2_O) to the infant as indicated above; baseline urine and post-dose samples will be collected after 24- and 48 h. All samples will be stored in 2 ml tubes at −80°C until analysis. Total milk intake and total body water will be estimated based on the measurement of deuterium enrichment by isotope ratio mass spectrometry (IRMS) [32, 34].

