### Hypotheses and outcome measures

Primary hypotheses: The use of a relaxation tape by breastfeeding mothers starting at week 2 postpartum will result in:i.reduced maternal stress and anxietyii.the production of a higher volume of breast milkiii.lower milk cortisol concentrationsiv.favourable effects on infant behaviour (less crying, more sleeping)v.differences in infant body composition

Measures (i) - (v) will be assessed at baseline (week 2) and at 12 weeks in both control and intervention groups to ascertain the long-term effects of the relaxation therapy. Measures of (iii) will also be assessed pre and post a single breast-feed in both groups at 2, 6 and 12 weeks to ascertain the short-term effects of the relaxation therapy. The primary comparison will be the values at 12 weeks adjusted for the baseline value, compared between the two groups. Measures of body composition (v) will also be assessed at 14–16 weeks postnatally.

The primary outcomes will be assessed as follows:i)maternal stress and anxiety assessed using the Cohen’s Perceived Stress Scale (PSS) and Beck Anxiety Inventory (BAI) respectively (at 12 weeks)ii)breast milk volume at 12 weeks assessed non-invasively using stable isotope techniquesiii)breast milk cortisol concentrations at 12 weeksiv)infant behaviour measured using a 3-day diary at 6 weeksv)infant weight and body composition measured using stable isotopes at 12 weekschanges in maternal saliva cortisol, breast milk cortisol and milk volume before and after a breastfeeding session at 2, 6 and 12 weeks.

b) Secondary hypotheses:i.Infant temperament, behaviour and gender influence milk intake and hence early growth and body composition.ii.Milk composition including non-nutrient factors in breast milk (hormonal constituents; ghrelin and leptin) influence infant appetite and feeding patterns and hence infant growth and body composition

The secondary outcome measures will be:i.non-nutrient factors in breast milk – leptin and ghrelinii.macronutrient composition and milk energy (fat, carbohydrate, protein and total calorie)iii.infant temperament measured using the Revised-Infant Behaviour Questionnaire (R-IBQ)iv.infant appetite assessed using the Baby Eating Behaviour Questionnaire (BEBQ)v.maternal depression assessed using Edinburgh Postnatal Depression Scale (EPDS

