### Sample size and study population

The target sample population will be first-time mothers and their newborn infants living in Klang-Valley, Malaysia. The conventional formula [15] for two sample t-test is used to determine the number of infants required to detect a difference between two groups; control and intervention:$$ \mathrm{n}=16\ \left({\mathrm{SD}}^2/{\mathrm{D}}^2\right) $$where *n* = number per group, *SD* = standard deviation, *D* = difference between groups.

Hence, a sample of 56 infants (28 per randomised group) would allow the detection of a 0.76 SD difference in milk volume between groups at 80% power with a significance level of α = 0.05 (D = 0.76, SD = 1); this is a biologically plausible difference based on previous studies of the effect of relaxation interventions on milk volume production between control and intervention groups of mothers with preterm infants [13]. Since this study will involve mothers with healthy full-term infants, the effect size may be smaller than the previous study, as mothers with preterm infants are likely to be more stressed. Therefore, to allow for a smaller effect size as well as for drop-outs or failed measurements, it is planned that 80–100 pregnant women will be recruited.

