##### Home visit I (HV1)

During HV1, the mother will be informed about the procedure for the visit and will be given a leaflet as a guide to the overall plan of the session. The mother will also be provided with a manual breast pump (Philips Avent brand) as a tool to express her breast milk sample if she wishes to use it. Mothers will also be shown how to use breast massage and hand expression techniques, which will allow her to choose the method she uses to express milk based on her preferences. Overall, during the first home visit, data will be collected from each mother-infant dyad as follows:Collection of data on birth experience and initial breastfeeding practice using the CDC Neonatal Questionnaire.Collection of data on breastfeeding practices and behaviour using an Infant Feeding Questionnaire (IFQ I), adapted from CDC and UK Infant Feeding Study 2010.Collection of data on infant appetite using the Baby Eating Behaviour Questionnaire (BEBQ).Infant weight, length and head circumference and maternal weight.Mothers randomised to the relaxation group will be provided with an mp3 with the relaxation therapy recording to use during the breastfeeding session. The purpose of the exercises and imagery will be explained to the mother. Details of the therapy are described below.Mini-breastfeeding test: The mother will be asked to collect samples of breast milk and saliva before and after a feed during the home visit without the presence of the researcher in the room. Mothers in the intervention group will be asked to listen to the relaxation/imagery recordings during this breast-feed. Prior to the feed, the mother will be asked (i) to collect a sample of her saliva to measure cortisol; (ii) to collect a sample of fore milk to measure cortisol, leptin, ghrelin and macronutrient content; (iii) to complete a questionnaire describing her feelings and emotions (Mini-breastfeeding Questionnaire). She will be asked to repeat these measures after completing the feed, including providing a sample of hind-milk; and to record the time and length of the feed. Mother’s saliva will be collected, and time and date will be recorded.The mother will be dosed with deuterium to measure infant breast milk intake using the stable isotope method. The mother will be given written and oral instructions on collecting her saliva and urine samples from the infant post-dose.The mother will be given a 3-day infant behaviour diary with instructions to complete after the visit; this will be collected at the next home visit.At the end of the first home visit, mothers will be given a set of questionnaires to assess maternal psychological state (Edinburgh Postnatal Depression Scale (EPDS; depression), Perceived Stress Scale (PSS; stress), Beck Anxiety Inventory (BAI; anxiety) to complete at their convenience; these will be collected at the next home visit.

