### Intervention tool: The relaxation therapy recording

Mothers in the intervention group will be provided with a relaxation therapy tape to be used during breastfeeding or when they express milk. The tape recording consists of a modified guided imagery protocol based on a CD designed for breastfeeding mothers [16], which has been used previously in a study of mothers with preterm infants [13, 14]. The recording was transcribed and translated into the Malay language, in collaboration with a certified clinical psychologist in UPM ([name]). Mothers in the intervention group will be asked to listen to an audio recording with relaxation therapy (either Malay- or English-version according to their preference) while breastfeeding during every home visit sessions (HV1–3). They will be informed that the purpose of listening to the tape is to make the mother relax during breastfeeding and that this may or may not have beneficial effects on breastfeeding outcomes, which is one of the aims of the study. They will also be asked to listen to the recording daily while breastfeeding or expressing milk for at least 2 weeks starting at HV1 and again at HV2 and HV3. In between visits (from HV1 to HV3), they will be advised to keep using the relaxation therapy daily, as often as they find it useful, and will be given a calendar diary to record when it is used.

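### The baseline milk volume is measured after randomisation while the intervention arm is using the recording, so adjusting the 12-week comparison for it shrinks the estimate if the recording acts early

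*Protocol article*

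**What the plan says.** **Timing.** Under Randomisation, mothers are allocated before HV1. Under Home visit I (HV1), the intervention arm receives the recording and plays it during the feed at that visit. The Intervention tool section asks these mothers to "listen to the recording daily while breastfeeding or expressing milk for at least 2 weeks starting at HV1 and again at HV2 and HV3".

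**Milk volume.** Under Collection of isotope samples: "Milk volume will be measured at 2–4 week (as baseline data at HV1) and 12–14 week (at HV3) using stable isotopes". The mother is dosed at HV1 and samples follow up to day 14. The Discussion describes the result as intake over a 14-day period.

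**Analysis.** Under Hypotheses and outcome measures: "The primary comparison will be the values at 12 weeks adjusted for the baseline value, compared between the two groups". Milk volume is among the measures listed as assessed at baseline. The Plan of statistical analysis repeats the rule for the main intention-to-treat analysis: final outcome adjusted for baseline where available, using independent t-tests. Neither section exempts milk volume.

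**Other measures.** On the diary: "The mother will be given a 3-day infant behaviour diary with instructions to complete after the visit". PSS, BAI and EPDS are handed over at the end of HV1, completed at the mother's convenience and collected at the next visit.

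**The concern.** A baseline covariate is safe to adjust for because treatment cannot have changed it. Here the baseline window and the first requested two weeks of daily listening coincide, so one arm is on treatment throughout and the other is not. Only the day-0 enrichment samples precede dosing, and they do not measure milk volume.

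If the recording has already raised intake in that window, the adjustment credits part of the treatment effect to the covariate and removes it from the estimate. The protocol gives reasons to expect an early effect. It lists the change in milk volume across a single feed at 2, 6 and 12 weeks among its outcomes, and its Background proposes an immediate mechanism through milk ejection. The request for daily listening is also the same after HV1 as after HV3, so intended use in the two isotope windows is similar.

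Milk volume is the only outcome with a sample size calculation, so the adjustment affects the comparison for which the trial was sized.

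**Working it through.** **1. Reproduce the stated sample size.** The article says "The conventional formula [15] for two sample t-test is used to determine the number of infants required" and concludes that "a sample of 56 infants (28 per randomised group) would allow the detection of a 0.76 SD difference in milk volume between groups". Its formula gives 16 × 1²/0.76² = 27.7, rounded up to 28 per group. Power from the non-central t with 28 per group is 79.8%. The figure is right, and it refers to an unadjusted comparison.

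**2. Effect of the adjustment.** Let D = 0.76 be the true 12-week effect in SD units, f the share of D already present in the week 2–4 value, and r the within-arm correlation of the two values (equal SDs). The documents give neither f nor r, so both are assumed ranges.

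- ANCOVA estimates D(1 − r·f).
- Its standard error is about √(1 − r²) × √(2/n + (fD)²/(2(n − 1))). The second term arises because the covariate now differs between arms.
- A change score estimates D(1 − f).

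Example with r = 0.5, f = 0.5, n = 28:

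- Estimate: 0.76 × 0.75 = 0.57 SD.
- Standard error: 0.866 × √(0.0714 + 0.1444/54) = 0.236.
- Normal-approximation power: Φ(0.57/0.236 − 1.96) ≈ 68%. Simulated ANCOVA, which allows for the t distribution, gives 65%.

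**3. Results: expected ANCOVA estimate, with simulated power, 28 per arm**

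| r | f = 0 | f = 0.25 | f = 0.5 | f = 1 |
|---|---|---|---|---|
| 0.3 | 0.76 SD, 83% | 0.70 SD, 76% | 0.65 SD, 68% | 0.53 SD, 48% |
| 0.5 | 0.76 SD, 89% | 0.67 SD, 79% | 0.57 SD, 65% | 0.38 SD, 32% |
| 0.7 | 0.76 SD, 97% | 0.63 SD, 89% | 0.49 SD, 69% | 0.23 SD, 19% |

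The comparator is the unadjusted 12-week contrast: 0.76 SD and 80% power, whatever f is.

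**4. If the adjustment is a change score.** The article says the adjusted comparison will use independent t-tests, which may mean a t-test on change. The whole share f is then lost: 0.76 × 0.5 = 0.38 SD at f = 0.5, and zero at f = 1.

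**5. Other measures.** The first diary, PSS and BAI are completed after HV1 and so after the recording has been introduced. The behaviour outcome is set at 6 weeks and there is no 12-week diary, so for the diary the problem arises through the general rule of adjusting the final value for baseline. By contrast, HV1 fore-milk and pre-feed saliva are collected before the feed at which the recording is played, and infant weight is taken before the feed. Those are usable as baselines.

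**The case against.** The size of the problem is unknown. It needs both a positive f and a positive r. If the effect builds only after week 4, nothing is lost and the covariate improves precision (89% against 80% power at r = 0.5). At f = 0.25, power is about kept at r = 0.5 and is higher than unadjusted at r = 0.7. The f = 1 column is a worst case. All of this stands. It limits the expected loss of power, but the estimate is attenuated for any f above zero.

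A reader might infer more than the documents support:

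- **That randomisation is undone or the test is invalid.** If the recording has no effect on milk volume, the HV1 value does not depend on arm and the adjusted test keeps its type I error. The harm is attenuation, conditional on an early effect.
- **That a null result could not be interpreted.** The analysis plan already includes t-tests and repeated-measures analyses of milk intake between groups and time points as secondary analyses. These could reveal an early difference and hence over-adjustment. They do not repair the primary comparison.
- **That the sample size is wrong.** It reproduces exactly for the unadjusted test.
- **That listening is compulsory.** Mothers are asked to listen daily, so actual exposure may be lower than intended.

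**Conclusion.** The point holds as an error in the primary comparison as written. The timing follows directly from the article: the milk volume labelled baseline is a post-randomisation, on-treatment value in the intervention arm, and no earlier milk volume is available. Adjusting for it reduces the expected estimate by the fraction r·f under ANCOVA, or by f under a change score. Within the assumed ranges (r from 0.3 to 0.7, f from 0 to 1), a true 0.76 SD is estimated at between 0.76 and 0.23 SD, with power between 97% and 19%. Where in that range the trial lies cannot be determined from the document. The direction, towards zero, rests on a positive correlation between the two measurements and on some effect of the recording in the first two weeks.

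**What to change.** In Hypotheses and outcome measures, Collection of isotope samples, and Plan of statistical analysis:

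1. Stop calling the week 2–4 milk intake a baseline, and remove it from the primary comparison.
2. Compare 12-week milk volume between arms unadjusted, or adjusted only for variables fixed before the recording is used: ethnicity stratum, infant sex, and birth weight or pre-feed HV1 infant weight.
3. Report week 2–4 milk intake by arm as an early outcome.
4. Apply the same rule to the first 3-day diary (for the 6-week behaviour outcome) and to PSS and BAI, unless these are completed before the recording is handed over. EPDS, a secondary outcome with the same timing, should follow.

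**Cost.** For milk volume this changes wording only and needs no new data. If the early effect is negligible, a useful covariate is given up: power falls from about 89% to 80% at r = 0.5, and from 97% to 80% at r = 0.7. The stated 80% is kept, because the sample size was calculated for an unadjusted test. The document does not say how strongly the substitute covariates correlate with milk volume, so no gain from them should be assumed.

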#### Analysis of biological samples

Breast milk samples will be analysed to determine the hormonal (cortisol, leptin and ghrelin) and macronutrient content. The macronutrient content of breast milk will be analysed using the MIRIS analyser at UCL. The breast milk cortisol, leptin & ghrelin will be measured by commercially available kits for enzyme-linked immunosorbent assay (ELISA) using cortisol saliva human ELISA, leptin human ELISA and ghrelin acylated & total human ELISA kits, respectively.

### Plan of statistical analysis

Data that are later found to be ambiguous will be flagged up and re-checked, and mothers will be contacted for clarification where necessary. Data will be recorded initially in Excel datasheets and later exported to SPSS. All questionnaires and anthropometric data will be analysed using IBM SPSS (version 23). Normality of continuous data will be assessed by Q-Q Plot, histogram and will also be tested by the Kolmogorov-Smirnov Test. The main analysis will be an intention-to-treat analysis comparing the difference between groups in the final outcome adjusted for the baseline value where data are available using independent t-tests. Independent t-test and repeated measures will be used to examine changes in milk intake and other milk components including cortisol levels between groups and between time points respectively as secondary analyses. For the secondary outcomes, associations between infant temperament/behaviour and milk volume, milk composition, infant growth and body composition will be examined using univariate analyses. Correlation and regression analysis/MANOVA will then be used to adjust for confounding factors. Interaction terms will be introduced where appropriate, especially in the multivariate analysis. The cut-off used for significance will be set at *p* < 0.05. Although multiple testing will be done to test the outcomes, the *p*-value cut-off point will not be adjusted for multiplicity since the different outcome measures are independent of each other.

Anthropometric data will be converted to standard deviation score (SDS, Z-score) for infant weight, height, head circumference and BMI using WHO 2006 standard data (LMS growth add- in for Microsoft Excel) and SDS will be used in all analyses. The weight data at the final time point will be compared between groups and adjusted for baseline weight as the primary outcome measure for growth using the LMS ‘Weight gain to SDS’ based on the WHO 2006 growth standard data (ie. external data). This method takes into account the baseline weight (HV1) in calculating the change from baseline to an endpoint or increase in weight between two-points of measurements. An increment of more than 1 band on the WHO growth chart or ±0.67 SD between measurements will be considered as representing ‘rapid weight gain’ [35].

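### The milk-volume comparison could gain precision cheaply by also adjusting for infant sex and infant weight at the first home visit

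*Protocol article*

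**What the plan says.** - **Sizing.** Under Sample size and study population, the target is the "detection of a 0.76 SD difference in milk volume between groups at 80% power", from an unadjusted two-sample t-test formula. This gives "a sample of 56 infants (28 per randomised group"). Milk volume is the only outcome with a stated calculation.
- **Main comparison.** Hypotheses and outcome measures sets the primary comparison as the 12-week value adjusted for its baseline. Plan of statistical analysis repeats this as an intention-to-treat analysis "comparing the difference between groups in the final outcome adjusted for the baseline value where data are available" and names independent t-tests as the method. Adjustment for confounders by regression is planned only for the secondary association analyses.
- **Infant sex.** One secondary hypothesis reads: "Infant temperament, behaviour and gender influence milk intake and hence early growth and body composition".
- **Infant weight.** The HV1 list includes "Infant weight, length and head circumference and maternal weight". The Infant weight section says weighing takes place ahead of the breastfeeding session. Birth weight is an eligibility item in Table 1.

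**The concern.** The outcome is the infant's total milk intake in absolute terms. A larger infant can be expected to take more, although no passage says so, and the investigators themselves hypothesise a sex effect. If either is prognostic, its variance stays in the error term of the one comparison the trial is sized on. The sample size section concedes that the effect in mothers of term infants may be smaller than the one used, so precision matters here.

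The data are in hand. HV1 weight precedes the first use of the recording. Sex is not listed as a data item, but neither the sex hypothesis nor scoring against the WHO growth standard can be carried out without it.

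**Working it through.** **Inputs from the protocol article.** D = 0.76, SD = 1, 28 per group, 80% power, "significance level of α = 0.05" (Sample size and study population). Sidedness is not stated; the factor 16 implies two-sided.

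**Assumed inputs, not in the documents.** R² is the share of variance in 12-week milk volume explained by sex and HV1 weight, taken as 0 to 0.20. The correlation between baseline and 12-week milk volume is taken as 0.5.

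**Step 1: reproduce the plan.** n = 16 × SD²/D² = 16/0.76² = 27.7, so 28 per group. The t-test non-centrality is 0.76/√(2/28) = 2.844 on 54 degrees of freedom, giving power 0.798. The stated 80% reproduces.

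**Step 2: add sex and weight, no baseline adjustment.** With k covariates:
- residual SD = √(1 − R²)
- degrees of freedom = 2n − 2 − k
- variance inflation for chance covariate imbalance = (2n − 3)/(2n − 3 − k)
- non-centrality = D / [residual SD × √(2/n) × √inflation]

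For n = 28 and k = 2, there are 52 degrees of freedom and the inflation is 53/51 = 1.039. At R² = 0.10, for example, the non-centrality is 0.76/(0.949 × 0.267 × 1.019) = 2.94, giving power 0.823.

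| R² | Power at 0.76 SD | Detectable difference at 80% power |
|---|---|---|
| no covariates | 0.798 | 0.762 SD |
| 0 | 0.782 | 0.778 SD |
| 0.05 | 0.802 | 0.758 SD |
| 0.10 | 0.823 | 0.738 SD |
| 0.20 | 0.864 | 0.696 SD |

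Break-even is close to R² = 0.05. At a smaller effect of 0.60 SD (chosen for illustration), power is 0.597 without covariates and 0.602, 0.625 and 0.676 at R² of 0.05, 0.10 and 0.20.

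If the 64 dyads given under Study design are analysed as 32 per arm, power at 0.76 SD is 0.849 without covariates and 0.855, 0.873 and 0.908 with them.

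**Step 3: add sex and weight on top of a clean baseline.** The residual SD with baseline alone is √(1 − 0.5²) = 0.866. With k = 1 at 28 per arm, power is 0.891. Adding two covariates (k = 3, inflation 53/50 = 1.06) gives:

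| Share of remaining variance explained | Power at 0.76 SD |
|---|---|
| baseline alone | 0.891 |
| 0 | 0.879 |
| 0.05 | 0.894 |
| 0.10 | 0.910 |
| 0.20 | 0.938 |

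The change runs from about −1 to +5 points.

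**Step 4: is the baseline clean?** Collection of isotope samples places the first milk-volume measurement over the 14 days after the HV1 dose. The intervention tool section asks mothers to use the recording daily over at least the same two weeks. Suppose a share f of the effect is already present then. The baseline-adjusted effect becomes D(1 − 0.5f). With f = 0.5 (assumed), that is 0.76 × 0.75 = 0.57 SD, and power is 0.668 rather than 0.891. Sex, birth weight and HV1 weight do not share this overlap.

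**The case against.** The strongest reply is that nothing here is an error. The randomised comparison is valid without these covariates, the stated power reproduces, chance imbalance is already reflected in the confidence interval, and a longer covariate list could sit in an analysis plan. All of that stands, except that the article does not leave the matter open: it names the main comparison and its one covariate.

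The second reply is that baseline milk volume, measured by the same method in the same infant, already carries much of what sex and weight would add. This stands in part and is why step 3 shows smaller gains. It is weakened by the overlap in step 4, and by the naming of independent t-tests, which cannot themselves adjust for a baseline value.

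A reader might infer three stronger things that the documents do not support:
- **That the protocol states sex determines milk intake.** It is a secondary hypothesis, still to be tested.
- **That the powered comparison is biased or underpowered by the omission.** Omitting a prognostic covariate from a randomised comparison of means costs precision only, and the stated power never relied on these covariates.
- **That a known amount of precision is lost.** No R² is given. Below about 0.05 the adjustment gains nothing, and gains measured from the unadjusted 80% overstate what is added if a clean baseline adjustment is in fact made.

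**Conclusion.** The point holds as a low-cost improvement, not as a flaw. At 28 per arm and 0.76 SD, the gain is about 0 to 7 points of power without baseline adjustment (0.798 to 0.802–0.864). On top of a clean baseline it is about 0 to 5 points (0.891 to 0.894–0.938). Both ranges rest on an assumed 5 to 20% of variance explained, and the second also on an assumed correlation of 0.5. If the covariates explain nothing, the loss is 1.6 points without baseline adjustment and 1.2 points with it. The downside is small and bounded. The possible gain is larger, and these covariates precede use of the recording, whereas baseline milk volume is measured while it is in use.

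**What to change.** In Plan of statistical analysis, pre-specify a linear model for 12-week milk volume on randomised group, infant sex and infant weight at HV1 (or birth weight), alongside whatever baseline adjustment is kept. Report the estimate without sex and weight as a sensitivity analysis. Fix the choice before outcome data are seen, so that it cannot be driven by an observed imbalance. List infant sex explicitly as a data item.

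The cost is one line of the plan and two degrees of freedom. No new measurement is needed, and the sample size statement can stay as it is.

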## Methods/Design

### Study design

This is a randomised controlled trial that involves first-time healthy breastfeeding (BF) mothers and their full-term infants (*n* = 64 mother-infant dyads). The objective is to identify causal effects of maternal psychological state, manipulated using a relaxation intervention on breast milk volume and composition and infant outcomes (behaviour and growth). In general, this study investigates the mother-infant signalling during breastfeeding and aims to provide a greater understanding of maternal-infant factors which influence the breastfeeding outcomes such as milk yield or milk energy, and which may be useful targets for future interventions.

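### The first-step association analyses carry no term for randomised arm, and arm is not named for the adjusted step, so a tape effect on both variables of a pair can appear as a link between them

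*Protocol article*

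**What the plan says.** Under Plan of statistical analysis, the protocol article describes the secondary analyses in two steps. First, associations of infant temperament or behaviour with "milk volume, milk composition, infant growth and body composition will be examined using univariate analyses". Second, "Correlation and regression analysis/MANOVA will then be used to adjust for confounding factors", with interaction terms where judged appropriate. No confounder is listed, and randomised arm is neither included nor excluded. No within-arm or control-only analysis is described. The cut-off is p < 0.05, and "the *p*-value cut-off point will not be adjusted for multiplicity since the different outcome measures are independent of each other".

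Under Hypotheses and outcome measures, the primary hypotheses begin "The use of a relaxation tape by breastfeeding mothers starting at week 2 postpartum will result in" and go on to list, among other effects, more breast milk, lower milk cortisol, less crying and more sleeping, and a difference in infant body composition. The secondary hypotheses then state that infant temperament, behaviour and gender act on milk intake and so on growth and body composition, and that milk constituents act on appetite, feeding pattern, growth and body composition.

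The only effect size in the document is under Sample size and study population: "a sample of 56 infants (28 per randomised group) would allow the detection of a 0.76 SD difference in milk volume". The same section says the effect may be smaller in mothers of term infants.

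**The concern.** Several variables on both sides of the secondary associations are variables that the trial expects its own intervention to change. If the tape raises milk volume and also reduces crying, mothers in the tape arm will tend to have more milk and calmer infants, and mothers in the control arm the reverse. A correlation computed over all dyads then picks up the difference between arms, even if milk volume and crying are unrelated among mothers treated alike.

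The secondary hypotheses are worded causally: one feature of the dyad influences another. A correlation that exists only because both variables respond to the tape is not evidence for such a link. The more effective the tape, the less an unadjusted association says about the secondary hypothesis. The Background justifies the experimental design by the difficulty of separating cause from effect in observational data; a first step without arm brings part of that difficulty back.

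**Working it through.** **Inputs from the protocol article.** 28 infants per group, 56 in total, D = 0.76 and SD = 1, 80% power, α = 0.05 (Sample size and study population); 64 dyads (Study design); 80 to 100 women recruited in pregnancy (Sample size and study population); p < 0.05 (Plan of statistical analysis).

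**Inputs assumed.** The effect on the second variable of each pair, and any milk-volume effect other than 0.76 SD; equal arms; normal variables with within-arm SD 1; no within-arm correlation.

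**The plan's own figure.** n = 16 × SD²/D² = 16/0.76² = 16/0.5776 = 27.7, rounded up to 28 per group. This reproduces; the exact t-test power at 28 per group is 79.8%.

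**Correlation induced by arm.** If the tape shifts the two variables by d₁ and d₂ SD and there is no link within arms, equal allocation gives a between-arm covariance of d₁d₂/4 and variances of 1 + d₁²/4 and 1 + d₂²/4. So

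r = (d₁d₂/4) / √[(1 + d₁²/4)(1 + d₂²/4)]

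- 0.76 and 0.76: 0.1444/1.1444 = 0.126
- 0.76 and 0.5: 0.095/√(1.1444 × 1.0625) = 0.086
- 0.5 and 0.5: 0.0625/1.0625 = 0.059
- 0.76 and 0.3: 0.057/√(1.1444 × 1.0225) = 0.053
- 0.3 and 0.3: 0.0225/1.0225 = 0.022
- 0 and 0.76: the numerator is 0, so r = 0

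**False-positive rate at p < 0.05**, from 40,000 simulated trials per setting:

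| Tape effect on the two variables (SD) | n = 56, no arm term | n = 64, no arm term |
|---|---|---|
| 0 and 0.76 | 5.0% | 5.1% |
| 0.3 and 0.3 | 5.3% | 5.5% |
| 0.76 and 0.3 | 6.8% | 7.1% |
| 0.5 and 0.5 | 7.3% | 7.5% |
| 0.76 and 0.5 | 9.7% | 10.3% |
| 0.76 and 0.76 | 15.4% | 17.0% |

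With arm as a covariate, the rate lies between 4.8% and 5.2% in every setting and the mean correlation is about 0.

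**Hand check of the last row.** By Fisher's transformation, atanh(0.126) ≈ 0.127. At n = 64, 0.127 × √61 ≈ 0.99, and the chance of exceeding ±1.96 is about 0.166 + 0.002 = 0.168. At n = 56, 0.127 × √53 ≈ 0.92, giving about 0.150 + 0.002 = 0.152. Both agree with the simulation.

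**Larger samples.** With 0.76 SD on both variables the rate would be 20% at n = 80 and 24% at n = 100. These are outer limits, because the 80 to 100 are women recruited in pregnancy, not dyads analysed. They show that a larger sample makes the artefact worse, since it is a bias and not noise.

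**The case against.** A reader might infer that the whole association analysis pools the arms with no arm term. The article does not say that. Its second step adjusts for confounders that it does not name. Arm is a confounder on the reasoning above, so it may be among them, and a condensed article may leave the covariate list to a fuller plan that is not shown. This objection stands for the adjusted step. It does not reach the first step, which is stated to be univariate and so has no place for arm.

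A reader might also take 15% to 17% as the error rate for the secondary hypotheses. That is not supported either. The figure applies only to the unadjusted step, and the article does not say that conclusions are drawn from that step alone. It also needs 0.76 SD on both variables, whereas the document gives that size for milk volume only and warns that it may be too large. It is near the top of the plausible range.

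A further objection concerns mechanism. The Background describes a chain from maternal state to milk production to infant feeding behaviour and growth. If the tape reached growth only through milk, the absence of a within-arm link between milk and growth would mean no tape effect on growth by that route, and the rate would stay at 5%. This holds for fully mediated pairs. The artefact needs the tape to move the two variables by separate routes, which is possible for crying and milk volume, for example.

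Finally, not every pair is exposed. Gender cannot respond to the tape, and temperament, appetite, leptin and ghrelin are not in the list of primary effects, although the Abstract speaks more generally of altered milk composition. Where the tape moves only one variable of a pair, nothing is induced.

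**Conclusion.** The point holds in a limited form. The stated first step has no arm term, and arm is not named for the second. For pairs drawn from milk volume, milk cortisol, infant behaviour and body composition, the trial's own primary hypotheses make arm a possible common cause. With no within-arm link and 56 to 64 dyads, the excess over the nominal 5% is negligible at 0.3 SD on both variables, about 2 percentage points at 0.5 SD on both, about 5 points at 0.76 and 0.5 SD, and 10 to 12 points at 0.76 SD on both. These sizes rest on an assumed effect for the second variable, on separate routes from the tape to each variable, and on reading the unadjusted result as evidence.

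The primary comparison between randomised groups is not affected. This is a small, worthwhile improvement to a secondary analysis and not an error that threatens the trial's main results.

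**What to change.** State that randomised arm enters every association model from the first step on, as a partial correlation given arm or a regression with arm as a covariate, and as a factor wherever MANOVA is used. State also that conclusions on the secondary hypotheses rest on the arm-adjusted estimates. Unadjusted correlations can still be shown if labelled descriptive.

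Arm is assigned at random, so it can be neither a consequence of the variables studied nor a step between them. Adjusting for it removes the part induced by arm and keeps any real within-arm link. The cost is one degree of freedom (at n = 64, residual degrees of freedom fall from 62 to 61) and no new data. Adding the ethnicity stratum or an arm-by-exposure interaction to every model is optional; the calculations here give no support for requiring either.
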